### Preoperative work-up

All patients will complete symptom and quality-of-life assessments for GORD health-related quality of life (GERD-HRQL)^41^, gastrointestinal health (structured assessment of gastrointestinal symptoms scale; SAGIS)^42^ and overall health (Short-Form Six-Dimension version 2; SF-6Dv2)^43,44^. All patients will undergo global health screening and optimization of medical co-morbidities. There will be a focus on obesity-related conditions (for example, type 2 diabetes mellitus (fasting blood sugar level and glycated haemoglobin (HbA1c)), cardiovascular disease (cardiac risk assessment, 12-lead ECG ± echocardiogram ± exercise stress testing), non-alcoholic fatty liver disease (liver function tests ± abdominal ultrasound), obstructive sleep apnoea (STOP-BANG questionnaire ± sleep physician review),^45^ and nutrition (clinical assessment and protocolized blood tests)), with operating risk scoring conducted with the Elixhauser score^46,47^.

All patients will undergo blood tests to assess nutritional and hormonal parameters, oesophago-gastro-duodenoscopy (OGD) with oesophageal biopsy, 24-h pH and impedance study, solid-state high-resolution oesophageal manometry (reporting using the Chicago IV classification), breath tests (gastric emptying and small intestinal bacterial overgrowth), and bladder pressure measurements. To minimize patient discomfort and achieve the most reliable results, the bladder pressure measurement will be performed at the time of OGD while under sedation. The ambulatory pH probe will be placed at the conclusion of the OGD, again under sedation to minimize discomfort.

In keeping with enhanced recovery after surgery (ERAS) principles^48^, both patient groups will receive operation-specific preoperative counselling about their procedure and recovery interval including expectation setting regarding usual milestones of recovery. All patients will receive counselling and printed literature (pre-existing through Metro South Dietetics service) on how to implement a very-low-calorie diet for 2 weeks before surgery, which can achieve up to 80 per cent reduction in hepatic steatosis^49^.

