### Objectives

The primary objective is to determine if there is a difference in treatment success (defined as a reduction of 50 per cent of more in the GERD-HRQL score between the preoperative value and the 1-year value) following LRYGB compared with LF (as used in two contemporary high-impact GORD treatment RCTs^59,60^).

With this respect, the trial was design according to the following hypotheses:

*H_0_*: Postoperative GORD symptom scores (GERD-HRQL) will be similar for patients undergoing LRYGB *versus* LF for GORD at 1 year.
*H_A_*: Postoperative GORD symptom scores (GERD-HRQL) will be different for patients undergoing LRYGB *versus* LF at 1 year.

The secondary objectives are to determine any differences in terms of:

Treatment success at 5 years (decrease of 50 per cent of more in the GERD-HRQL score between the preoperative value and the 5-year value)Objective measures of GORD at 1 and 5 yearsNon-GORD gastrointestinal symptom scores at 1 and 5 yearsOverall health at 1 and 5 years

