For participants in both control and treatment groups, outcomes will be measured at baseline, 1 year and 5 years after surgery. The primary outcome is GORD symptom scores (assessed with the GERD-HRQL survey). Secondary outcome(s) are GORD symptom scores (assessed with the GERD-HRQL survey) at 5 years, the percentage of total time spent with pH < 4 in the oesophagus, the presence and severity of oesophagitis, and patient-reported outcomes. Gastrointestinal-specific quality of life will be assessed using the SAGIS questionnaire^42^ (including dysphagia, belching, bloating, flatulence, and altered bowel habit), while overall quality of life will be assessed using SF-6Dv2^43,44^. The operative metrics and surgical morbidity measures will be operating time (measured in minutes), pain score (measured using a visual analogue score and oral morphine equivalents), length of hospital stay (measured in days), the Comprehensive Complication Index^61^, the development of complicated gallstone disease, and readmission rate (at 90 days). Bodyweight changes will be monitored. With respect to the changes in pathophysiological parameters contributing to GORD, the transient lower oesophageal sphincter relaxation episodes and duration on high-resolution manometry and bladder pressure measurement (as a surrogate for intra-abdominal pressure) will be measured both before and after surgery.

For randomization, an adaptive procedure will be used to stratify patients according to sex, BMI (class I or uncomplicated class II), and percentage of time with oesophageal pH < 4 (4–10 per cent and more than 10 per cent), with the use of a ‘biased coin’ procedure to balance treatment assignments^60^. The symmetric Kullback–Leibler divergence minimization method, which allows the use of both continuous and categorical factors will be used^62^. A 1:1 assignment will be used with a block size of six. The goal is that the patient will be kept blinded until after the operation. To achieve this, group allocation will be performed by a database manager (non-clinician) the morning before surgery (to facilitate operating room scheduling and equipment preparation). It will be directly communicated to the operating surgeon.

For blinding, the allocation sequence will be concealed from researchers responsible for assigning participants. The patient will be kept blinded until after the operation. Where possible, data analysis will be conducted in a blinded fashion.

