### Statistical considerations

There are limited data to guide the sample size calculation. A pilot phase of 20 patients (10 in each arm)^63^ will be completed at the Upper Gastrointestinal Surgery Unit, Princess Alexandra Hospital. This will allow an assessment of recruitment rate and an analysis of the primary outcome to enable the power calculations and trial duration to be recalculated and ensure that the trial remains practical and can be completed. In addition, any initial logistical issues can be resolved. Thereafter, the trial will be extended across Logan Hospital, QEII Jubilee Hospital and the Royal Brisbane and Women’s Hospital.

The trial will be powered based on the primary outcome alone. Using *α* = 0.05, *β* = 0.8, a randomization ratio of 1: 1 and a mean(s.d.) GERD-HRQL score of 8(8) after LF in class I and II obesity^64^ and 5 after LRYGB^65^, a sample size of 164 would be required. Assuming a 10 per cent dropout, there would need to be 91 patients in each arm. This equates to approximately 2 years of referrals of eligible patients to the Princess Alexandra Hospital alone. Assuming participation of the other hospitals and 50 per cent uptake, a conservative estimate is that recruitment will take approximately 3 years.

Acknowledging the lack of data to guide power calculations and hence the possibility that the alternative treatment (LRYGB) may give the same mean GERD-HRQL score as the control treatment (LF), a planned non-inferiority analysis will also be performed. Using *α* = 0.05, *β* = 0.9, a randomization ratio of 1: 1, a mean(s.d.) GERD-HRQL score of 8(8) after LF in class I and II obesity and a non-inferiority limit (d) of 4, a sample size of 138 is required. Assuming a 10 per cent dropout, there would need to be 77 patients in each arm.

Given that both superiority and non-inferiority analyses are planned, it is appropriate to perform both intention-to-treat and per-protocol analyses. Continuous data will be tested using a Student’s *t* test if data are normally distributed or otherwise a Mann–Whitney *U* test. Normality of continuous data will be assessed with the Shapiro–Wilks test. Categorical data will generally be assessed using the chi-squared test or Fisher’s exact test when the assumptions of the chi-squared test are not met. All *P* values will be two-tailed (except for non-inferiority analysis), and significance will be set at 0.050.

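### The plan names only unadjusted two-sample tests, which are valid but give up precision available from the baseline GERD-HRQL score and the minimisation factors.

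*Protocol article*

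**What the plan says.** Under Statistical considerations, the protocol article sets the tests by type of data: "Continuous data will be tested using a Student’s *t* test if data are normally distributed or otherwise a Mann–Whitney *U* test", and "Categorical data will generally be assessed using the chi-squared test or Fisher’s exact test". The sample size in the same section compares two postoperative means, 8 and 5, with SD 8. No section mentions regression, ANCOVA, a stratified test or any other adjustment.

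Two other sections supply information that these tests do not use:

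- Preoperative work-up: "All patients will complete symptom and quality-of-life assessments for GORD health-related quality of life (GERD-HRQL". A baseline value of the outcome measure is therefore planned for everyone.
- Outcomes, in the randomization paragraph: "an adaptive procedure will be used to stratify patients according to sex, BMI (class I or uncomplicated class II), and percentage of time" (the last factor being acid exposure). The method is "The symmetric Kullback–Leibler divergence minimization method, which allows the use of both continuous and categorical factors will be used", combined with a biased coin.

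The article describes the primary outcome in two ways. Outcomes states "The primary outcome is GORD symptom scores (assessed with the GERD-HRQL survey", a continuous score, and the power calculation follows this. Objectives speaks of treatment success, "defined as a reduction of 50 per cent of more in the GERD-HRQL score between the preoperative value and the 1-year value", which is a yes/no outcome.

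**The concern.** Two kinds of precision are lost if the 1-year score is compared by a plain t test or Mann–Whitney test.

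First, the baseline score of the same instrument may predict the 1-year score. A test that leaves it out counts the variation it explains as noise.

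Second, minimisation makes the arms more alike on sex, BMI class and acid exposure than chance would. If these factors predict outcome, the treatment difference varies less from trial to trial than the unadjusted standard error supposes. The test then rejects less often than its nominal 5%, and the confidence interval is too wide. The design controls these factors at allocation and the stated analysis does not use them.

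The stake is efficiency: wider intervals than necessary for the superiority comparison and for the non-inferiority comparison against the 4-point limit.

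**Working it through.** **Inputs from the article (Statistical considerations).** Means 8 and 5 (difference 3), SD 8, 1:1 allocation, two-sided α 0.05, 164 patients before dropout (82 per arm). For non-inferiority: limit 4, one-sided α 0.05, power 90%, 138 patients.

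**Assumed inputs.** The correlation r between baseline and 1-year score, and the share R² of outcome variance explained by the balancing factors, are not given. The ranges below are assumptions.

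**1. The plan's own figures.** The number per arm is n = 2 × SD² × (z₁ + z₂)² / difference².

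- Superiority: 2 × 64 × (1.960 + 0.842)² / 9 = 111.6, so 112 per arm and 224 in total. The stated 164 is not reproduced. A one-sided test gives 176, which does not match either.
- Non-inferiority: 2 × 64 × (1.645 + 1.282)² / 16 = 68.5, so 69 per arm and 138 in total. This is reproduced.

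**2. Power of the unadjusted test at 82 per arm.** Standard error = 8 × √(2/82) = 1.249, and 3 / 1.249 = 2.40. Two-sided power is 66.5% from the t distribution (67.0% from the normal approximation).

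**3. Adjustment for baseline.** Residual SD = 8 × √(1 − r²). Power is from the t distribution, and the 95% half-width is 1.96 × SD × √(2/82).

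| Assumed r | Residual SD | Power | Half-width |
|---|---|---|---|
| 0 | 8.00 | 66.5% | 2.45 |
| 0.2 | 7.84 | 68.3% | 2.40 |
| 0.3 | 7.63 | 70.6% | 2.34 |
| 0.5 | 6.93 | 78.7% | 2.12 |
| 0.6 | 6.40 | 84.7% | 1.96 |

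The shortfall from 80% is 80 − 66.5 = 13.5 points. At r = 0.3 adjustment returns 70.6 − 66.5 = 4.1 of them. At r = 0.5 it returns 12.2.

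**4. Actual size of the unadjusted test.** With near-perfect balance on the factors, the size is 2 × [1 − Φ(1.96 / √(1 − R²))].

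- R² = 0: 5.0%
- R² = 0.1: 1.96 / 0.949 = 2.066, giving 3.9%
- R² = 0.2: 1.96 / 0.894 = 2.191, giving 2.8%

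**5. Simulation.** Biased-coin minimisation on three binary factors, 164 patients and 2,000 runs per setting, agrees in direction. It used a simple marginal imbalance rule with a coin probability of 0.8 (assumed), not the Kullback–Leibler method itself. With R² = 0.2 the unadjusted test rejected a true null in 2.3% and 3.2% of runs, and its intervals covered the truth in about 97–98%. With R² = 0 it rejected in 6.0% and 5.1% of runs, consistent with 5% given a simulation standard error of about 0.5 points.

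**6. Non-inferiority at 82 per arm, unadjusted.** 4 / 1.249 = 3.20; 3.20 − 1.645 = 1.56; power is about 94%.

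**The case against.** Five points can be made for the plan as written.

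- **The sentence on tests is general.** It covers every continuous outcome and does not single out the primary one, and an analysis plan that is not shown could add covariates. That is fair, and it limits how firmly the primary analysis can be called unadjusted. But the article states which tests will be used, and they are unadjusted. The point concerns that stated choice and offers a better one, so it does not rest on missing detail.
- **Baseline is not ignored if treatment success is the primary outcome.** This stands. A reader might infer that the plan discards baseline in every case. Under the responder definition in Objectives, baseline is part of the endpoint, and none of the power figures above applies. Only the omission of the minimisation factors remains.
- **The benefit is assumed.** This also stands. At r = 0.2 or 0.3 the gain is small. If the balancing factors do not predict outcome, the unadjusted test keeps its nominal size.
- **The low power has another cause.** A reader might blame the roughly 67% power on the choice of test. It arises because 164 does not follow from the stated inputs, and the article already plans to recalculate power after the pilot. Non-inferiority has no such shortfall.
- **The score may be skewed.** A mean of 8 with SD 8, on a score that presumably cannot be negative, suggests that the normality rule could lead to Mann–Whitney. The t-based power figures do not describe that route. Mann–Whitney is also unadjusted, however, and gives no mean difference to set against the 4-point limit.

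**Conclusion.** The point holds as one of efficiency. The stated tests do not use the baseline score or the three balancing factors, although all are collected. For the continuous 1-year score this costs precision and, where the factors are prognostic, makes the test conservative.

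The documents do not support a claim of bias or of false positive findings: any departure from nominal size is in the cautious direction. Nor do they support a claim that adjustment would restore the planned power. Depending on an assumed r from 0.2 to 0.6, the gain at 82 per arm runs from about 2 to 18 percentage points, and 80% is reached only in the upper part of that range. The sizes of 3.9% and 2.8% need near-perfect balance and an assumed R² of 10% or 20%.

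The change is worth making because a few prespecified covariates cost very little in 164 patients even if they prove weak. The sample-size error needs its own correction.

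**What to change.** If the continuous score is primary, prespecify an ANCOVA of 1-year GERD-HRQL on treatment, baseline GERD-HRQL, sex, BMI and percentage time with pH < 4. Report the adjusted mean difference with its confidence interval, and use that one estimate for both superiority and non-inferiority (at the confidence level each test requires).

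If the responder outcome in Objectives is primary, compare the arms with adjustment for the minimisation factors, for example by logistic regression. Baseline is already in that definition.

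Hospital may be added, but this is optional because it is not a balancing factor.

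The cost is a few lines of analysis text. No extra patient, visit or measurement is needed. The recalculation planned after the pilot is a natural time to make the change. Until a correlation is available, the sample size should not count on the gain.

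### The normality pre-test sends the primary GERD-HRQL score to Mann–Whitney, but both sample sizes and the 4-point non-inferiority limit are set on mean scores

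*Protocol article*

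**What the plan says.** All of the sizing is in the protocol article, Statistical considerations. Superiority rests on "a randomization ratio of 1: 1 and a mean(s.d.) GERD-HRQL score of 8(8) after LF in class I and II obesity" "and 5 after LRYGB", a difference of 3 points in means. Non-inferiority uses the same control mean and s.d. with "a non-inferiority limit (d) of 4, a sample size of 138 is required". The stated reason for it is that the two operations might turn out to have equal mean scores.

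The same section gives one rule for continuous data: Student's t test "if data are normally distributed or otherwise a Mann–Whitney" U test. The gate is "Normality of continuous data will be assessed with the Shapiro–Wilks test". No exception is made for the primary score. P values are two-tailed except for non-inferiority, at 0.050. No mean-difference estimate is named, and nothing says how the 4-point limit is to be tested on the Mann–Whitney branch.

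On the endpoint, Outcomes states: "The primary outcome is GORD symptom scores (assessed with the GERD-HRQL survey". Objectives states both hypotheses on scores at 1 year, but opens with a responder definition (a halving of the score): "The primary objective is to determine if there is a difference in treatment success".

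**The concern.** The sample sizes and the non-inferiority limit are in points of mean score. The test rule is driven by a normality pre-test that the protocol's own planning figures suggest the score will fail. The rule would then select a rank test, which addresses a different quantity and, in its plain form, contains no margin. At stake is whether the 90% power for non-inferiority belongs to the test that will be run, and whether a significant superiority result can be read as a difference in mean GERD-HRQL.

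**Working it through.** **Inputs from Statistical considerations.** LF mean 8, s.d. 8; LRYGB mean 5, s.d. not given; limit 4; 164 in total for superiority (82 per arm) and 138 for non-inferiority (69 per arm). The values printed as β (0.8 and 0.9) are read as power.

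**Assumptions, not in the document.** The score cannot fall below zero, its distribution is skewed (rounded gamma unless stated), and the LRYGB s.d. is varied.

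**1. The non-inferiority size is a comparison of means.** n per arm = 2 × s.d.² × (z₀.₉₅ + z₀.₉₀)² / d² = 2 × 64 × (1.645 + 1.282)² / 16 = 68.5, so 69 per arm and 138 in total, as stated. With 10% dropout, 69 / 0.9 = 76.7, so 77 per arm, as stated. The planned 90% power therefore belongs to a t-type test against 4 points.

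**2. The superiority size does not reproduce from its inputs.** With s.d. 8 in both arms, 2 × 64 × (1.960 + 0.842)² / 9 = 111.6, so 112 per arm and 224 in total, not 164. An LRYGB s.d. of about 5.5 comes close: (64 + 30.25) × 7.849 / 9 = 82.2 per arm. That is a separate matter; here it only shows where 5.5 comes from.

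**3. The gate.** For a normal score with mean 8 and s.d. 8, P(score < 0) = P(Z < −1) = 0.159. A score with a floor at zero cannot have 16% of its values below it, so it must be skewed. Shapiro–Wilk at the 5% level rejected as follows:

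| n per arm | Gamma, negative binomial, beta on 0–50, lognormal |
|---|---|
| 69 | 100% |
| 82 | 100% |
| 10 (pilot) | 38–49% |

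A milder half-normal shape at 82 was rejected in 99.9% of runs.

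**4. Non-inferiority, 69 per arm, one-sided 0.05, LF 8(8).** Gamma and beta shapes:

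| LRYGB truth | Plain Mann–Whitney | Mann–Whitney after subtracting 4 | Comparison of means against 4 |
|---|---|---|---|
| 8(8): equal arms | 4–6% | 98–99% | 89–90% |
| 12(8): difference at the limit | about 0% | 4–6% | 4–5% |
| 12(12): difference at the limit, wider spread | about 0% | 40–43% | 5–7% |

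The plain test asks whether LRYGB is better, so with equal arms it succeeds only at its error rate. The shifted test holds its error under a pure shift. It does not when the spreads differ, because a location shift is then not the mean difference.

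**5. Superiority, 82 per arm, two-sided 0.05, true means both 8, LF s.d. 8.**

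| LRYGB s.d. | Mann–Whitney rejects | Welch comparison of means rejects |
|---|---|---|
| 8 | about 5% | about 5% |
| 7 | about 8% | about 5% |
| 5.5 | about 25% | about 5% |

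The comparison of means keeps its error rate at this size without normality.

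**The case against.** Four points on the other side have weight.

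- **The hypotheses do not name means.** Objectives speaks of scores being similar or different. Mann–Whitney is a legitimate test of a difference in distributions, and with 8(8) against 8(5.5) the distributions do differ (gamma medians about 5.5 and 6.8). This stands. A reader might infer a 25% false-positive rate for superiority, but the documents do not support that. The figure counts as error only if the null is equal means, and it rests on an s.d. back-solved from 164 with an LRYGB mean of 5. At the only s.d. stated, 8, there is no inflation.
- **Superiority power is not shown to suffer.** In gamma simulations at 82 per arm, Mann–Whitney against Welch gave 82% and 82% for 8(8) v 5(5.5), 98% and 66% for 5(8), and 73% and 84% for 5(5). The direction depends on the assumed spread. This stands.
- **A rank method can carry a limit in points.** A shifted Mann–Whitney or a Hodges–Lehmann interval would do so, so it goes too far to say that non-inferiority cannot be tested at all. But the article states neither method, and neither targets the mean difference behind the 138.
- **The endpoint is itself in conflict.** If the responder definition in Objectives is the primary endpoint, the chi-squared rule applies and the gate does not touch it. This stands as a condition on the point, and the conflict needs its own reconciliation.

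It may also be said that this is detail for an analysis plan. Leaving the estimator to such a plan would be no fault. Here, however, the article fixes a rule, and that rule conflicts with its own sizing.

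**Conclusion.** The rule is wrong as written and should be fixed. Where the GERD-HRQL score is analysed as the primary outcome, the pre-test will in practice select Mann–Whitney at the planned size, while both sample sizes and the 4-point limit are on the mean.

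The clearest consequence is for non-inferiority: about 5% success with equal arms for the plain test against the planned 90%, or an unstated shifted version whose one-sided error can reach about 43% when the true mean difference is 4 and the spreads are 8 and 12. For superiority the consequence is one of interpretation, with rejection under equal means between about 5% and 25% over LRYGB s.d.s of 8 to 5.5.

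This depends on the score having a floor at zero and on the planning mean and s.d. being roughly right. A reader might also infer that the primary test stays open until the data are seen. On these figures it does not at full size, because the gate's result is all but certain. Only at the pilot's 10 per arm could it go either way.

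**What to change.** In Statistical considerations, exempt the primary score from the Shapiro–Wilk rule and state one analysis for both questions: the difference in mean 1-year GERD-HRQL (LRYGB minus LF) with a confidence interval that does not rely on normality or equal spread (Welch, sandwich standard errors or bootstrap). Read it against 0 for superiority and its upper limit against 4 for non-inferiority. Report Mann–Whitney as a sensitivity analysis. Use the same analysis on the pilot data that feed the power recalculation. Reconcile the responder definition in Objectives with the score in Outcomes, so that it is clear which endpoint this governs.

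The cost is one paragraph of wording, with no extra patients or data. The non-inferiority size of 138 already matches this analysis. The basis of the 164 has to be settled separately.

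### Oesophagitis severity is an ordered grade, but the only stated rule for categorical data ignores order; an ordered test would cost nothing and usually gain power

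*Protocol article*

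**What the plan says.** Under Outcomes, the protocol article lists "the presence and severity of oesophagitis" among the secondary outcomes. It does not say how severity is graded or how many grades there are. Endoscopy is done before surgery (Preoperative work-up) and again at 1 and 5 years (Postoperative care).

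Under Statistical considerations, the rule for categories is "Categorical data will generally be assessed using the chi-squared test", with Fisher's exact test as the substitute where the chi-squared assumptions fail. The rule for continuous outcomes is "Continuous data will be tested using a Student’s *t* test if data are normally distributed or otherwise a Mann–Whitney *U* test". No third rule covers ordered categories, and oesophagitis is not named in either rule. On size and error, the same section says "The trial will be powered based on the primary outcome alone" and that P "values will be two-tailed (except for non-inferiority analysis), and significance will be set at 0.050".

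**The concern.** Severity is ordered by its meaning, from none through mild to severe. Pearson's chi-squared and Fisher's exact test return the same P value however the grade labels are shuffled. They cannot tell a consistent move towards milder grades from scattered differences of the same size, and they spread the comparison over one degree of freedom fewer than the number of categories. A reader who follows the stated rule would test the grades this way, because the one rank test in the plan is kept for continuous data.

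At stake is the chance of detecting a real shift in severity. Endoscopic grade is one of the objective measures of reflux named in the secondary objectives. It is not self-reported, whereas the primary symptom score comes from patients who are to be kept blinded only until after the operation.

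**Working it through.** **The plan's own figure.** The article states no power for oesophagitis, so there is none to reproduce. The arm size used here is the stated evaluable number, 164 / 2 = 82. That 164 does not itself follow from its inputs: 2 × (1.960 + 0.842)² × 8² / 3² = 111.6, or 112 per arm. That is a separate matter; 82 is used here only as the planned size.

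**Inputs.**
- From the article: 82 per arm, two-sided 0.05, chi-squared with a switch to Fisher.
- Assumed: the number of categories (counting no oesophagitis as one), the control shares, and a proportional-odds shift towards milder grades in one arm.

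**Step 1, large-sample comparison.** Let an ordered test on 1 degree of freedom have noncentrality λ. An omnibus test on k − 1 degrees of freedom has at most about the same λ but a higher critical value: 3.84 on 1 df, 5.99 on 2, 7.81 on 3 and 9.49 on 4. For 80% ordered power, λ = 7.85.

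| Ordered test | 3 categories | 4 categories | 5 categories |
|---|---|---|---|
| 50% | 40% | 35% | 31% |
| 80% | 71% | 65% | 60% |
| 95% | 91% | 87% | 84% |

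The loss at 80% ordered power is therefore about 9, 15 and 20 points.

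**Step 2, simulation of the rule as written.** Tables with small expected counts go to Fisher (its extension to more than two categories); the others go to Pearson. The comparator is the tie-corrected Mann–Whitney test. The rows at odds ratios 2.0 and 2.5 use 1,500 trials each and switch when more than 20% of expected counts are below 5 or any is below 1. The rows at 2.2 and 2.6 use 3,000 trials and switch when any expected count is below 5. Monte Carlo error on a power is at most √(0.25/1500) = 1.3 points.

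| Assumed control shares, % | Odds ratio | Stated rule | Mann–Whitney | Loss, points |
|---|---|---|---|---|
| 70/20/10 | 2.0 | 38.4% | 48.1% | 9.7 |
| 70/20/10 | 2.5 | 56.2% | 66.9% | 10.7 |
| 60/20/15/5 | 2.0 | 39.4% | 56.3% | 16.9 |
| 60/20/15/5 | 2.5 | 61.8% | 78.1% | 16.3 |
| 70/15/10/4/1 | 2.0 | 33.5% | 47.2% | 13.7 |
| 70/15/10/4/1 | 2.5 | 50.4% | 67.5% | 17.1 |
| 80/10/6/3/1 | 2.0 | 21.9% | 34.1% | 12.2 |
| 80/10/6/3/1 | 2.5 | 35.9% | 52.3% | 16.4 |
| 75/11/8/4/2 | 2.2 | 32% | 48% | 16 |
| 75/11/8/4/2 | 2.6 | 44% | 62% | 18 |
| 65/15/12/6/2 | 2.2 | 41% | 61% | 20 |
| 65/15/12/6/2 | 2.6 | 56% | 76% | 20 |
| 50/20/15/10/5 | 2.2 | 51% | 73% | 22 |
| 50/20/15/10/5 | 2.6 | 69% | 84% | 15 |

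Pearson alone would overstate the loss in sparse tables. With 70/15/10/4/1 and odds ratio 2 it gives 27% against 47%, a loss of 20 points, where the stated rule loses 14.

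**Step 3, away from moderate effects.** At odds ratio 1.5 the rule loses 4.7 points with three categories, 6.6 with four and 6.4 to 8.1 with five. At odds ratio 4 it loses 5.9 and 5.6 with three and four. With five categories the loss at odds ratio 4 depends on how close the ordered test is to full power: 5 points for 50/20/15/10/5 (94% against 99%), but still 17.7 for 80/10/6/3/1 (61.9% against 79.7%).

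**Step 4, the presence test.** Chi-squared on presence (yes/no) against Mann–Whitney on grade, with the shift favouring treatment: 46% against 47% (70/15/10/4/1, odds ratio 2), 61% against 63% (65/15/12/6/2, odds ratio 2.2) and 69% against 72% (50% free of oesophagitis, odds ratio 2.2). If treatment is worse and 50% of controls are free of oesophagitis, presence falls about 9 to 11 points short. With five equally common categories and odds ratio 2 it has 49% against 70%.

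**Step 5, error rate.** With no true difference, rejection was about 3.5% to 5.5% across the tests. Neither approach is anti-conservative to any material degree.

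**The case against.** The strongest reply is that the article never assigns severity to this test. The rule is hedged by the word *generally*, no grading scale is given, and a full protocol or analysis plan that is not shown may name an ordered test. A reader might infer that the trial has committed itself to an unordered test of oesophagitis grade; the text does not go that far. What remains is that the article is not silent. It states one rule for categories, offers no exception, and keeps the rank test for another type of data. A rule that fits a listed outcome poorly can be criticised as written.

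A second reply is that the presence test, which is sound, already captures most of the signal. This stands where the shift favours treatment and most patients are free of oesophagitis. It does not stand where grades are spread more evenly or the shift runs the other way.

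A third is that the trial has no planned power for this outcome to lose. That is correct, and it limits the weight of the point without answering why the weaker test should be used.

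Not using the preoperative grade is no error: an unadjusted comparison is valid in a randomized trial, and the gain from adjustment has not been quantified.

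**Conclusion.** The point holds as a minor one. The stated rule, applied to ordered grades, discards the order and loses power. At 82 per arm and an odds ratio of about 2 to 2.6, the loss is roughly 10 points with three categories, 15 to 17 with four and 14 to 22 with five. One scenario with 80% of controls free of oesophagitis came to 12.

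A reader might infer a fixed loss of 15 to 25 points. The documents do not support that: the number of categories, their shares and the effect are all assumptions, the switch to Fisher recovers part of the loss in sparse tables, and three categories stay near 10. Nor do they support the inference that a real improvement in oesophagitis would usually be missed, because presence is also an outcome. Type I error is not inflated, and neither the primary outcome nor the sample size is affected.

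**What to change.** Add one sentence to Statistical considerations. Presence of oesophagitis will be compared by chi-squared or Fisher's exact test; severity grade will be compared by an ordered method, either a Mann–Whitney or linear-trend test or a proportional-odds model. Name the grading scale in the same place. If the model is chosen, keep the rank test as the fallback where proportional odds does not fit. Adjustment for preoperative grade is optional and uses data already collected. If a separate analysis plan already names an ordered test, the article's rule needs only a stated exception.

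The cost is that sentence. No extra patients, visits or data are needed, and there is no change to clinical care.
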